## Methods/design

### Study design and setting

Our study is a prospective, multicenter, subject-, assessor-, and analyst-blinded, pragmatic randomized controlled trial. The research period lasts from May 2015 to May 2020 (201507001-08). Five centers from five cities will be involved in recruitments, treatments, and assessments. Informed consent will be obtained after screening for eligibility, then baseline assessments will be conducted before randomization (details in Table 1). Eligible patients will be allocated, in a 1:1 ratio using a dynamic randomization procedure, into a BP-lowering acupuncture therapy group (experimental group) and a control group. After randomization, the patients in the experimental group will be additionally treated by the *HuoXueSanFeng* needling method (a BP-lowering regimen) plus the “*XingNaoKaiQiao*” needling method [34] (a formula for stroke) over 12 weeks, whereas the control group will be only given the *XingNaoKaiQiao* needling method for 12 weeks. Other routine ischemic stroke treatments in both groups will be provided. During the whole process of our study, the antihypertensive medications will be adjusted based on the BP level in the two groups (details displayed in the “Antihypertensive medication adjustment” section). The primary outcome will be all recurrent stroke cases over a follow-up period of 9 months after receiving 12-week acupuncture treatments. Our protocol presentation is in accordance with the Standard Protocol Items: Recommendations for Interventional Trials 2013 (SPIRIT 2013) guidelines. The study flowchart is presented as Fig. 1.

**Table 1 Tab1:** Study schedule

Period	Screening	Baseline	Treatment (weeks 1–12)		Follow-up (weeks 13–48)	
Week	Week 0	Week 0	Week 6	Week 12	Week 24	Week 48
Eligibility	×					
Demographic medical history	×					
Informed consent		×				
Basic laboratory test®	×			×	×	
24-h ABPM		×	×	×		
TCM syndrome score, SF-36		×	×	×		
NIHSS, BI		×	×	×		
ESRS		×				×
Follow-up BP					×	×
Recurrence of stroke						×
NO, ET, Hcy, sCD40L, Copeptin		×		×	×	
ECG		×		×	×	
Chest X-ray		×				
Color Doppler ultrasound®		×		×		
All-cause mortality rate						×
Combined diseases and drugs	Record at any time					
Antihypertensive medication adjustment	Record at any time					
Adverse event	Record at any time					
Daily BP	Record everyday (based on BP diary)					
Safety of acupuncture	Record at any time					
Patients’ compliance				×		

Basic laboratory test®: blood, urine, and stool routine, coagulation function, D-dimer, liver and kidney function. Color Doppler ultrasound®: cardiac ultrasound, carotid artery ultrasound, transcranial Doppler of lower extremities ultrasound. *ABPM* ambulatory blood pressure monitoring, *SF-36* Short Form 36-item Health Survey, *NIHSS* National Institute of Health Stroke Scale, *BI* Barthel Index, *ESRS* Essen Stroke Risk Score, *BP* blood pressure, *NO* nitric oxide, *ET* endothelin, *sCD40L* soluble CD40 ligand, *ECG* electrocardiograph, *Hcy* homocysteine, *TCM* traditional Chinese medicine

**Fig. 1 Fig1:**
[figure not shown]
Study flowchart®: *XingNaoKaiQiao* acupuncture + other routine ischemic stroke interventions + one class of antihypertensive drug. *ABPM* ambulatory blood pressure monitoring, *NIHSS* National Institute of Health stroke scale, *BI* Barthel Index, *ESRS* Essen Stroke Risk Score, *TCM* traditional Chinese medicine, *SF-36* the medical outcome study (MOS) 36-item Short Form Health Survey, *NO* nitric oxide, *ET* endothelin, *Hcy* homocysteine, *sCD40L* soluble CD40 ligand, *ECG* electrocardiogram

### Participants

We will recruit 480 eligible patients from (1) The First Teaching Hospital of Tianjin University of traditional Chinese medicine (TCM), (2) Longhua Hospital Shanghai University of Traditional Chinese Medicine, (3) Chongqing Traditional Chinese Medicine Hospital, (4) Mianyang Hospital of Traditional Chinese Medicine, and (5) Shenzhen Bao’An Traditional Chinese Medicine Hospital Group. The eligible patients must satisfy the criteria defined below. Patients who express a general interest in taking part in the study will meet with one of the study personnel to be informed of all necessary information in oral and written form. After fulfilling the criteria and signing the consent, the study personnel will assign the patient to the acupuncturist and the neurologist who is in charge of the patient.

### Inclusion criteria

Patients will be further screened for eligibility if they fulfill all of the following inclusion criteria: (1) first-ever ischemic stroke that has been confirmed by cranial computed tomography (CT) or magnetic resonance imaging (MRI), with stroke duration over 2 weeks and less than 6 weeks; (2) BP below 160/100 mmHg on using one antihypertensive medication except the fixed-dose combinations, for at least 2 weeks; (3) aged 35 to 70 years; and (4) voluntary informed consent signed.

### Exclusion criteria

Patients will be excluded if they have any one of the following: (1) secondary hypertension, (2) antihypertensive medication general use for reasons other than BP control, such as long-term need for beta-blockers or diuretics or non-dihydropyridine calcium channel antagonists for cardiac conditions, (3) BP below 140/90 mmHg when taking one hypotensive drug, (4) other coexisting nervous system diseases like epilepsy and peripheral nerve injuries, (5) severe hematopoietic system conditions, coagulation dysfunction, and cancers, (6) diabetic nephropathy, severe liver and renal function impairment, severe heart or lung dysfunction, and arrhythmia, (7) local infection at or around the acupoint, (8) pregnant or lactating women, and (9) recruitment into other clinical trials within 1 month.

### Ethical issues

Our protocol complies with the principles of the Declaration of Helsinki and has been approved by the central Independent Ethics Committee (IEC) of The First Affiliated Hospital of Tianjin University of Traditional Chinese Medicine (TCM) for the various centers (reference number: TYLL2016[K]NO.007). We have also registered at ClinicalTrials.gov (NCT02967484). The overall supervision of our trial will be in the charge of the central IEC of the First Affiliated Hospital of Tianjin University of TCM; any change in the protocol will be submitted to, and decided by, the Ethics Committee.

### Recruitment strategies

Firstly, all the patients will be enrolled from the inpatient departments of the acupuncture and moxibustion sections of each branch center, to fulfill the completion of the consistent acupuncture treatments for 6 weeks. We will also use advertisements, such as printed recruitment posters, in each participating hospital, and the various social media platforms to distribute the trial information.

### Informed consent

The details of our study, including trial objectives, characteristics, probable benefits and risks, other available treatment alternatives, and the subjects’ rights as well as obligations as stated in the Declaration of Helsinki, will be made clear to the patients by a study personnel who has their grouping code, and their agreement will be required. After obtaining the written informed consent, the subjects will be enrolled in the study.

During the process of the trial, if new points regarding the study ethics emerge, written revisions regarding the informed consent will be handled by the Ethics Committee and, after their approval, the individuals’ consent will be requested again. In case of the patients’ withdrawal, their available data will be kept for the final analyses.

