### Randomization and allocation concealment

All the eligible participants will be randomized into the experimental group or the control group, in a 1:1 ratio, using minimization, a dynamic random allocation technique by the MINIM program installed in each separate center. The baseline prognostic factors related to stroke recurrence, including age, categorized as 35–50, 51–65, and 66–70 years), gender, smoking status, diabetic status and atrial fibrillation, classified as “no” or “yes with/without anti-coagulation,” will be balanced between groups according to the minimization procedures. The computer-generated randomization grouping code will be offered after the recruitment of the eligible patients so that allocation concealment should be ensured.

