### Sample size and statistical methods

The sample size calculation of the study was based on China’s Ministry of Health data suggesting that at least 197 patients are required in each group for the final analysis to achieve a power of 80% to demonstrate a recurrence rate of 7%, rather than 16% resulting from *HuoXueSanFeng* acupuncture (data not shown, please see Additional file 1), at a two-sided significance level of 5%. Given a projected dropout rate of 15%, we aimed to recruit 480 patients for the study.

Statistical analysis will be conducted by a third party who is unaware of the treatment allocation. Data will be analyzed with SAS 9.1 and SPSS 19.0 software packages. Two-sided *P* < 0.05 represents statistical significance for all the analyses. Both intention-to-treat analysis (ITT) and per-protocol (PP) analysis will be performed. We will compare the result of ITT analysis with that of PP analysis to determine whether the results are consistent. For the ITT analysis, missing data will be handled by Last Observation Carry Forward rules, in brief, the finally observed data will be used for replacement of the missing primary variables.

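### The Informed consent section gives the recruiter the patients' grouping code, which conflicts with the protocol's only stated basis for allocation concealment

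*Protocol article*

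**What the plan says.** Four places in the protocol article bear on this.

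- **Informed consent.** The objectives, risks, alternatives and rights "will be made clear to the patients by a study personnel who has their grouping code", and the patient's agreement is then sought. The next sentence places enrolment after consent: "After obtaining the written informed consent, the subjects will be enrolled in the study".
- **Randomization and allocation concealment.** Patients are allocated 1:1 "using minimization, a dynamic random allocation technique by the MINIM program installed in each separate center". On concealment the section says: "The computer-generated randomization grouping code will be offered after the recruitment of the eligible patients so that allocation concealment should be ensured".
- **Study design and setting.** The order of steps is given as: "Informed consent will be obtained after screening for eligibility, then baseline assessments will be conducted before randomization".
- **Participants.** Study personnel inform interested patients, and then: "After fulfilling the criteria and signing the consent, the study personnel will assign the patient to the acupuncturist and the neurologist". The section does not separate those who recruit from those who hold or obtain the allocation.

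**The concern.** Allocation concealment requires that whoever decides to invite and enrol a patient cannot know the arm that the patient will receive. The consent section attributes the grouping code to exactly that person, at the step before enrolment. If this were done, the recruiter could let the known arm influence who is invited, how firmly borderline eligibility is judged, or how the trial is presented. Minimization on age, gender, smoking, diabetes and atrial fibrillation would keep those five factors balanced. It would not protect against selection on prognosis outside them, such as stroke severity or expected adherence. Blinding applied after allocation cannot undo selection that happened before it.

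**Working it through.** No figure in the plan depends on this point, so the check is a comparison of the texts.

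1. **Order of events.** The study design section gives screening, consent, baseline assessment, randomization. The consent section agrees that enrolment follows written consent.
2. **When a code can exist.** Under that order, and with release only after recruitment, nobody should hold a patient's code while the trial is being explained. The method points the same way: minimization computes the arm from the patient's own factors once they are entered, so a patient-specific code should not exist before entry.
3. **What the consent section adds.** It says that the person explaining the trial has the code. This fits neither the order in step 1 nor the release rule in step 2.
4. **Whether the term could mean something harmless.** A study identification number would be innocuous. But the randomization section uses the same term, grouping code, for the computer-generated treatment allocation, and the data management section describes the identifiers that protect personal information in different words. The text does not support the identifier reading.
5. **Whether another safeguard is stated.** The randomization section rests concealment on the timing of release alone. It describes "a dynamic random allocation technique by the MINIM program installed in each separate center" but does not say who operates the program. The article does not bar recruiting staff from the program or the code. The conflicting sentence therefore touches the only safeguard that is stated.
6. **Effect on the plan's numbers.** The planned comparison is "a power of 80% to demonstrate a recurrence rate of 7%, rather than 16"%. With pooled variance under the null and no continuity correction, n = [1.960·√(2·0.115·0.885) + 0.842·√(0.16·0.84 + 0.07·0.93)]² / 0.09² = (0.884 + 0.376)² / 0.0081 ≈ 196.1, rounded up to 197 per group, as the plan states. With 15% dropout, 197/0.85 gives 232 per group, or 464 in total, within the 480 planned. None of this changes: the issue is possible selection bias, not precision.

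**The case against.** The strongest reply is that the consent sentence is loose wording. It states no time, and having the code may describe the role of staff who receive it once it is issued. Two explicit statements elsewhere, and the way minimization works, point to a code that comes after consent. This stands in part: the evidence is one clause, not a described procedure that breaks concealment. It does not remove the conflict. The clause describes the person at the consent step and uses the protocol's own term for the allocation. Even on the mild reading, the same person recruits patients and later holds their allocations.

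A reader might also draw stronger conclusions that the documents do not support:

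- **That baseline NIHSS, Barthel Index or TCM scores would be rated with knowledge of the arm.** The outcome section says that the assessors are blinded, and the article does not say that the person taking consent rates these scales.
- **That installing MINIM locally is itself a fault.** It contradicts nothing, and who operates the program is a detail that a condensed article may leave to the full protocol. Its relevance is limited to the fix: access has to be controlled where the program is.
- **That steering a few patients would visibly move the result.** The planned difference is about 0.09 × 197 = 17.7 events per arm, but that is the hoped-for effect and not a measure of bias. A bias figure would need the number of patients steered and their excess risk, and the documents give neither.
- **That patient blinding is broken by this route.** No mechanism is described by which the recruiter's knowledge would reach the patient. The discussion already concedes, for other reasons, that some patients will probably know their group.

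**Conclusion.** The conflict is real and needs correcting. The consent section, as worded, is incompatible with the release rule in the randomization section and with the sequence in the study design section, and it concerns the only stated protection against selective enrolment.

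The conclusion rests on reading grouping code in the same sense in both sections, which the text supports, and on taking the consent sentence as describing the person at the time of consent, which is its plain sense but is not stated explicitly. If it is a slip, a short correction settles it. If it describes practice, concealment is lost wherever the practice is followed. The documents do not show which is the case, do not show that selective enrolment occurs, and do not allow the size of any bias to be estimated. The stated design, allocation after consent and baseline, is sound; the fault is a sentence that contradicts it.

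**What to change.** Rewrite the sentence in the Informed consent section so that it agrees with the other two sections:

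- Staff who judge eligibility and take consent have no access to the allocation or to the MINIM program until consent is signed, baseline assessment is complete and enrolment is recorded.
- At each center, MINIM is run by a named role that takes no part in recruitment or outcome assessment.
- That role is neither the research assistant who enters data masked to allocation nor the third-party analyst who is unaware of it. Moving code release to the data-management unit without separating roles could endanger that masking, so it is better kept with a separate person at the center.

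The cost is small: a corrected sentence, a separation of roles among existing site staff, and a short wait for each allocation. Sample size, visits and analysis do not change. If patients have already been enrolled, the sponsor should also record which practice was actually followed at each center, because the documents cannot settle that.

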### Randomization and allocation concealment

All the eligible participants will be randomized into the experimental group or the control group, in a 1:1 ratio, using minimization, a dynamic random allocation technique by the MINIM program installed in each separate center. The baseline prognostic factors related to stroke recurrence, including age, categorized as 35–50, 51–65, and 66–70 years), gender, smoking status, diabetic status and atrial fibrillation, classified as “no” or “yes with/without anti-coagulation,” will be balanced between groups according to the minimization procedures. The computer-generated randomization grouping code will be offered after the recruitment of the eligible patients so that allocation concealment should be ensured.

### Interventions (Table 2)

**Table 2 Tab2:** Protocol form

Item	Control group	Experimental group
Aim	To testify the efficacy of the acupuncture method of *HuoXueSanFeng* on stroke recurrence among ischemic stroke patients with hypertension	
Interventions	1 type of antihypertensive drug (may be adjusted based on the BP levels) + *XingNaoKaiQiao* acupuncture method + other routine care for stroke	*HuoXueSanFeng* acupuncture method + *XingNaoKaiQiao* acupuncture method + 1 type of antihypertensive drug (may be adjusted based on the BP levels) + other routine care for stroke
Intervention time	Continuous treatment period: 6 times a week, 6 weeks Consolidation treatment period: three times a week, 6 weeks	
Observation time	Before treatment, 6 weeks, 12 weeks, 24 weeks, and 48 weeks after treatment	
Researchers	To ensure the optimal effects of acupuncture stimulation, our therapists will be required to have clinical experience of acupuncture treatments for at least 8 years	
Materials	Disposable, sterile needles, 0.25 mm in diameter and 40 mm in length (HWATO, Suzhou, China)	

*BP* blood pressure

Both groups receiving acupuncture treatments ensures the blinding of subjects.

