### Experimental group

Patients in the experimental group will be given HuoXueSanFeng acupuncture therapy, in addition to the control group interventions. To ensure the optimal effects of acupuncture stimulation, all the therapists are required to have clinical experience of acupuncture treatments for at least 8 years.

Disposable, sterile needles with a diameter of 0.25 mm and a body length of 40 mm (HUATO, Suzhou, China) will be used. Patients are asked to adopt the supine position. Acupoints used here are bilateral *Renying* (ST9), *Hegu* (LI4), *Quchi* (LI11), *Taichong* (LR3), and *Zusanli* (ST36). The acupoint locations with reference to the World Health Organization (WHO) standards in the Western Pacific Region, and the corresponding manipulations of the aforementioned acupoints are listed in Table 3, which accord with those described in a previous paper [32]. All the manipulations will be applied for 1 min and the needles are retained for 30 min.

**Table 3 Tab3:** Acupoint form

Treatment methods	Points	Location	Acupuncture method
Acupuncture method of *HuoXueSanFeng*	*Renying* (ST9)	In the neck next to the thyroid cartilage, the anterior border of sternocleidomastoid, at the common carotid artery pulsation site	Using the twisting technique of the reinforcing method of the second definition from [name] academician, namely low amplitude (torsional amplitude less than 90°), high-frequency (120–160 times/min), the operation lasting for 1 min
	*Hegu* (LI4)	In the back of the hand, between the first and second metacarpals, at the midpoint of the second metacarpal radially	Using the twisting technique of the first definition of the reducing method from [name], academician
	*Taichong* (LR3)	In the dorsum of the foot, at the head of the first metatarsal space	Using the twisting technique of the first definition of the reducing method from [name], academician
	*Quchi* (LI11)	In the lateral end of the cubital crease, at the midpoint of the ligature between the end point of the cubital crease and the lateral epicondyle of the humerus with the elbow bent	Using the twisting technique of the first definition of the reinforcing method from [name], academician
	*Zusanli* (ST36)	In the anterior lateral of crus, 3 B-cun under *Dubi* (ST35), one transverse finger width from the anterior tibial border	Using the twisting technique of the first definition of the reinforcing method from [name], academician

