### Control group

The control group will receive one antihypertensive medication on the basis of ischemic stroke routine care. In our trial, basic ischemic stroke medical care includes 12 weeks of *XingNaoKaiQiao* needling therapy plus other forms of routine stroke care. Twelve weeks of *XingNaoKaiQiao* needling therapy should also aid in the improvement of compliance in both groups for its high acceptance and remarkable effectiveness for stroke. All medications must be recorded in the drug combination form, including the types, dosage, usage frequency and time, etc., in order to provide data for analysis and the report summary. The acupuncture needle is the same with that used in *HuoXueSanFeng* acupuncture treatments. The acupoint locations and manipulations are presented in Table 3. No common acupoints are used in the two formulas. The retention time and frequency of treatments are identical to *HuoXueSanFen*g acupuncture therapy. During the entire process of our study, the control-group patients are prohibited from receiving any BP-lowering acupuncture therapy, and any violations will be recorded.

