### Antihypertensive medication adjustment

After randomization, an electronic BP machine and a BP diary notebook will be delivered to all patients for measuring and recording their BP levels. During the first 6-week inpatient treatments, they will be instructed how to use the machine accurately. BP will be measured within 1 h after morning waking before taking antihypertensive medications, at 3 h after taking antihypertensive medications, at 4 p.m. and before bedtime over the entire process. On each occasion, three repeated measurements of supine BP, following a rest of at least 15 min, will be conducted at 1-min intervals. The antihypertensive medication classes in both groups will be recorded. Lifestyle advice regarding hypertension and stroke will be given to the patients. In the experimental group, if the patients have a mean BP level below 140/90 mmHg for three consistent days, they will receive solely acupuncture treatment; thereafter, once their BP levels increase to ≥ 140 mmHg systolic and/or ≥ 90 mmHg diastolic for 1 month, prior antihypertensive medications should be re-dispensed. Otherwise, if BP levels are ≥ 160 mmHg systolic and/or ≥ 100 mmHg diastolic for three consistent days after initiating *HuoXueSanFeng* acupuncture treatments or over the follow-up period, additional antihypertensives should be prescribed. All the medication adjustments will be filled out in the Case Report Forms (CRFs).

For the control group, when the average systolic BP increases to ≥ 160 mmHg and/or diastolic BP ≥ 100 mmHg lasting for three continuous days in the study period, other antihypertensive drugs will be prescribed in the opinion of the treating physicians, and these will be documented for final analyses.

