The acupuncture method of *XingNaoKaiQiao* for the treatment of stroke was launched in 1972 by the first, and to date, only Chinese academician of engineering in the acupuncture discipline, [name], who devoted himself to introducing acupuncture to the whole world and developed an international academic team that cooperates with Germany, France, Japan, and Singapore, among other countries. For its internationally substantial contributions, *XingNaoKaiQiao* needling therapy for stroke has been recognized as another special acupuncture technique in addition to acupuncture anesthesia by foreign health care researchers. Besides the confirmed effects for stroke by our own team, the others also reported its encouraging results for stroke patients [38]. With the great success of *XingNaoKaiQiao*, academician [name] gained deeper insight into secondary stroke prevention, and established another acupuncture treatment for hypertension called *HuoXueSanFeng*, the BP-lowering acupuncture regimen used in our trial. Our previous researches have shown that this acupuncture method reduces BP for primary hypertension patients, and its immediate and long-term antihypertensive efficacy is significant for either BP-lowering or improving the patients’ clinical symptoms [27–33]. So, here we also want to investigate the BP-controlling effect of *HuoXueSanFeng*, especially regarding its sole efficacy, in a larger sample size population. In this study, both *XingNaoKaiQiao* and *HuoXueSanFeng* needling therapy are performed over the 12-week treatment period; *XingNaoKaiQiao* therapy is a general treatment for stroke with a high credibility, its free treatment here will enhance adherence with participation. Additionally, because both groups are needled, subject blinding should be ensured, minimizing the placebo effect of acupuncture.

Of note, in our trial, we cautiously selected three secondary endpoints, namely, Hcy, sCD40L, and copeptin levels, which were closely related to stroke recurrence. Elevated Hcy levels have been reported to be indicative of an increased risk for ischemic strokes and recurrent strokes [39]. sCD40L appears to be an independent predictor for stroke recurrence [40]. Copeptin has been studied to be a predictor of both severity at admission and 1-year stroke recurrence in stroke patients [41]. Assessing the influence of our study treatment on them might be reflective of the effects on stroke recurrence via acupuncture lowering hypertension.

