The multicenter approach of our study allows more generalisable interpretation of the results and the usage of standardized, cross-culturally adapted assessment allows comparison and pooling of all study data from different trial centers. Considering methodological and ethical reasons, acupuncture will be delivered to both groups to prevent bias through potential placebo effects. To improve operation and observation consistency, the research sets strict rules that must be followed.

The unavoidable weaknesses of our trial are as follows: (1) the five hospitals are located in different cities, so the standard of acupuncture manipulation will differ between them. Therefore, strict training and supervision will be implemented to ensure unified and consistent operation as far as possible, (2) despite the subject- and assessor-blinding, there are still some patients who will likely know which group they are in; therefore, we would keep the patients separate when receiving treatment to avoid them talking to each other; (3) after completion of the 12-week treatment, a 9-month follow-up will be conducted. This time span means that participant compliance could be a problem. Accordingly, we have designed the BP diary and regular telephone follow-up to try to minimize this.

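### The protocol says that needling both arms ensures subject blinding, but arm-specific needling and arm-specific drug cessation mean that patients are not reliably blinded

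*Protocol article*

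**What the plan says.** The Methods paragraph of the Abstract gives the blinding label, and Study design and setting repeats it: "Our study is a prospective, multicenter, subject-, assessor-, and analyst-blinded, pragmatic randomized controlled trial". The reason stands below Table 2 in Interventions: "Both groups receiving acupuncture treatments ensures the blinding of subjects". The Discussion argues again that, since both arms are needled, "subject blinding should be ensured, minimizing the placebo effect of acupuncture". A later Discussion paragraph says that giving acupuncture to both groups prevents bias from placebo effects.

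The same article describes what differs between the arms. Experimental patients receive HuoXueSanFeng "acupuncture therapy, in addition to the control group interventions". Of that formula the Experimental group section says "Acupoints used here are bilateral" and lists ST9, LI4, LI11, LR3 and ST36. The Control group section adds: "No common acupoints are used in the two formulas". Under Antihypertensive medication adjustment, experimental patients whose mean BP stays below 140/90 mmHg for three days stop the drug: "they will receive solely acupuncture treatment". The control arm has only a rule for adding drugs at 160/100 mmHg.

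Finally, the Discussion's list of weaknesses admits that "there are still some patients who will likely know which group they are in". Its remedy is to keep patients apart while they are treated.

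**The concern.** Needling both arms hides the fact of being needled. It does not hide whether a patient receives the add-on under test. The protocol treats the first as if it secured the second, and then builds a conclusion about placebo effects on it.

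At stake are the outcomes that pass through the patient. SF-36 and the TCM syndrome score depend on the patient's own report, and diary BP is self-measured four times a day for the whole study. Stroke recurrence, the primary outcome, is followed up by monthly telephone call, and Data management and quality control lists direct questions to patients as one data source. A reader who accepts the blinding claim would give differences on these outcomes more credit than the design earns.

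**Working it through.** The plan gives no figure on blinding, so there is none to reproduce. The check sets out what a patient in each arm can perceive.

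| Feature | Control arm | Experimental arm | Source |
|---|---|---|---|
| XingNaoKaiQiao formula | yes | yes | Table 2 |
| HuoXueSanFeng formula | no; no sham described | yes | Table 2; Experimental group |
| Needling on the neck | none listed | ST9, at the carotid pulse | Table 3 |
| Retention time and session frequency | same | same | Control group |
| Drug stopped below 140/90 mmHg | no such rule | yes, after three days | Antihypertensive medication adjustment |
| Drug added from 160/100 mmHg | yes | yes | Antihypertensive medication adjustment |

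**Needling.** Five bilateral points give 5 × 2 = 10 extra sites per session. The schedule is 6 sessions × 6 weeks + 3 sessions × 6 weeks = 36 + 18 = 54 sessions. Experimental patients therefore have 10 additional sites at each of 54 sessions, with nothing corresponding in the control arm. Only retention time and frequency are matched.

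**Drug cessation.** The Background presents stopping the drug as the difference between the groups. It cannot be hidden from the patient to whom it happens. Whether that patient can infer the arm depends on knowing that cessation belongs to one arm. The Informed consent section says that the trial's objectives and characteristics are explained, but the consent text is not shown.

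**The two statements on blinding.** Under Table 2, subject blinding is secured. In the list of weaknesses, some patients will probably know their group. Both cannot stand. Separation during treatment limits comparison of needle sites between patients, but it does nothing about a drug being stopped.

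**Outcomes exposed.** Table 1 places SF-36 and the TCM syndrome score at baseline, week 6 and week 12. Diary BP runs throughout. The 24-h ambulatory recording depends less on the patient, but it ends at week 12, so it cannot stand in for diary BP during weeks 13–48.

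**The case against.** The strongest reply is that the limitation is disclosed. The Discussion names imperfect patient blinding as an unavoidable weakness and offers a mitigation, and its own claim there is worded more softly than the sentence under Table 2. Each patient also sees only one regimen. Someone who does not know the other arm's formula may not be able to name the arm from the needle sites. Table 2 describes the drug in both arms as adjustable to BP, so a patient told to stop it need not recognise this as specific to one arm.

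Much of this stands. The needling difference alone is the weaker ground, and four stronger readings that a reader might infer are not supported:

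- *Blinding is impossible, and every patient whose drug is stopped knows the arm.* That depends on consent wording that is not shown.
- *The assessors are unblinded too, because the telephone calls cover BP control and drug advice.* The Follow-up section does not say who calls, and Outcome assessments states that assessors are blinded.
- *The primary comparison is biased by a definite amount.* No document gives the share of patients unblinded or the size or direction of any reporting difference. Recurrent stroke is less open to expectation than SF-36, and medical records and relatives are also data sources.
- *The Discussion's remark that bias from placebo effects is prevented rests on blinding.* That sentence rests on both groups receiving acupuncture. Only the earlier Discussion sentence links blinding to the placebo effect.

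Disclosure does not settle the matter, because the label and the placebo argument are kept alongside it.

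**Conclusion.** The claim that subject blinding is ensured is not supported and contradicts the article's own list of weaknesses. The supported description is that patients are not reliably blinded. This rests on two stated differences between the arms, the added formula without a described sham and the arm-specific drug cessation, and on the article's own concession. Cessation carries more weight, since the patient must know of it and the Background names it as the difference between the groups.

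The size cannot be given: the share of patients who could identify their arm is not stated and cannot be derived. Assessor and analyst blinding are not refuted. The point should be corrected because it governs how the patient-dependent outcomes are read; it does not by itself invalidate the primary comparison. No view is taken on the drug rule.

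**What to change.** 1. Reconcile the Abstract, Study design and setting, the note under Table 2 and the Discussion with the Background, the two arm descriptions, the medication adjustment section and the list of weaknesses. Withdraw the subject-blinded label and the statements that blinding is or should be ensured. Describe the trial as assessor- and analyst-blinded, with patients not reliably blinded.
2. Drop the conclusion that placebo effects are minimised or prevented.
3. Interpret SF-36, TCM syndrome score and self-measured diary BP as outcomes without reliable patient blinding.
4. Add one treatment-guess question at the existing week 12 visit and report it by arm. The answer may also reflect the patient's own BP readings, so it describes the extent of unblinding and not its cause.
5. Classify recurrent stroke from the medical records already listed as a data source, without sight of drug-change data.

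The first three changes are wording and interpretation. The fourth is one item on the case report form, and the fifth uses a source already collected. The price is a less favourable description of the design. Neither arm's treatment changes.
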